## Abstract

**Background:**

Understanding how brain circuit dysfunctions relate to specific symptoms offers promise for developing a brain-based taxonomy for classifying psychopathology, identifying targets for mechanistic studies and ultimately for guiding treatment choice. The goal of the Research Domain Criteria (RDoC) initiative of the National Institute of Mental Health is to accelerate the development of such neurobiological models of mental disorder independent of traditional diagnostic criteria. In our RDoC Anxiety and Depression (“RAD”) project we focus trans-diagnostically on the spectrum of depression and anxiety psychopathology. Our aims are a) to use brain imaging to define cohesive dimensions defined by dysfunction of circuits involved in reactivity to and regulation of negatively valenced emotional stimulation and in cognitive control, b) to assess the relationships between these dimension and specific symptoms, behavioral performance and the real world capacity to function socially and at work and c) to assess the stability of brain-symptom-behavior-function relationships over time.

**Methods and design:**

Here we present the protocol for the “RAD” project, one of the first RDoC studies to use brain circuit functioning to define new dimensions of psychopathology. The RAD project follows baseline-follow up design. In line with RDoC principles we use a strategy for recruiting all clients who “walk through the door” of a large community mental health clinic as well as the surrounding community. The clinic attends to a broad spectrum of anxiety and mood-related symptoms. Participants are unmedicated and studied at baseline using a standardized battery of functional brain imaging, structural brain imaging and behavioral probes that assay constructs of threat reactivity, threat regulation and cognitive control. The battery also includes self-report measures of anxiety and mood symptoms, and social and occupational functioning. After baseline assessments, therapists in the clinic apply treatment planning as usual. Follow-up assessments are undertaken at 3 months, to establish the reliability of brain–based subgroups over time and to assess whether these subgroups predict real–world functional capacity over time. First enrollment was August 2013, and is ongoing.

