## Methods and design

We use a baseline-follow up design. Intensive assessments for all measures of interest are undertaken at the baseline session and after 12 weeks participants are re-assessed at follow-up on the symptom and functional outcome measures (Table 1). We control for medication-free status at the baseline session and record in an observational (rather than experimental) manner any interventions that participants were exposed to in the 12-week period between baseline and follow up. Because this was not an intervention study, but rather an investigation of the natural stability of brain-behavior-symptom relationships over time we do not control treatment type or intensity. Our clinical center partners use a structured treatment planning approach based on integrative psychotherapy principles with pharmacological augmentation and all participants recruited from the center are currently receiving individual therapy.

**Table 1 Tab1:** A summary of the test-retest design and type of data collected at each assessment time point

Screening	Baseline	Follow-up
Self-reported symptoms	Structured Clinical interview	
Contraindications for medication	Brain imaging of circuits	
	Behavioral performance	
Contraindications for brain imaging	Self-reported symptoms	Self-reported symptoms
Other contraindications for study participation	Self-reported and observer-rated coping, social and occupational function	Self-reported and observer-rated coping, social and occupational function

Participants are free of antidepressant medications and other medications that could impact the brain imaging assessments.

Consistent with the goal of RDoC and characterizing brain imaging-derived (rather than diagnostic) constructs, screening and exclusion criteria are kept to a minimum. We do not exclude for cognitive indicators of potential mild cognitive impairment (MCI) given that such cognitive deficits in many patients are associated with their anxiety and mood symptoms but are not indicative of neurodegeneration (for review; [43]). These indicators are recorded for inclusion as covariates in analyses.

For participants who meet inclusion criteria and are not screened out by exclusion criteria we schedule a testing site visit. At the testing site visit brain imaging, behavioral and self-report/observer-rated assessments are completed (Table 1).

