### Follow-up outcome measures

At 12-week follow-up, we assess change in/stability of symptoms using the PSWQ, DASS and MASQ, HPQ and WHOQoL.

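### The abstract says follow-up will establish the reliability of brain-based subgroups over time, and stability of brain-behavior relations is also promised, but imaging and behavioral tests are done only once

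*Protocol article*

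**What the plan says.** **Promised.** The Abstract (Methods and design) says that the 3-month follow-up is done "to establish the reliability of brain–based subgroups over time". It gives a second purpose as well, whether the subgroups predict real-world functional capacity. Aim (c) in the Abstract (Background) is "to assess the stability of brain-symptom-behavior-function relationships over time". The main Methods and design section describes the study as "an investigation of the natural stability of brain-behavior-symptom relationships over time", and the title of Table 1 calls the design test-retest.

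**Scheduled.** The same Methods and design section says that "after 12 weeks participants are re-assessed at follow-up on the symptom and functional outcome measures". In Table 1 the entry "Brain imaging of circuits" and the entry for behavioral performance stand in the baseline column, with nothing beside them under follow-up. The Follow-up outcome measures section says that at 12 weeks "we assess change in/stability of symptoms using the PSWQ, DASS and MASQ, HPQ and WHOQoL".

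**Objective and analysis.** The Secondary objective is whether circuit-defined dimensions predict change in symptoms and function. Item 4 of the Statistical analysis section covers change or stability of symptoms and function, and whether baseline imaging predicts them at 12 weeks.

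**The concern.** The subgroups are defined by imaging: high versus low on each circuit measure, or data-derived clusters. Establishing their reliability over time means classifying the same people twice. No second scan is scheduled, so the purpose that the Abstract names first for the follow-up visit has no data to answer it. The stability of the brain-behavior link has the same gap on both sides, because neither the scan nor the behavioral tests are repeated.

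This matters because the project aims at a circuit-based taxonomy and individual profile reports, and the background suggests that one type may be trait-like. Whether a person stays in the same subgroup is central to such claims. The wording should not leave readers expecting evidence on it from this study.

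**Working it through.** The plan gives no figure to reproduce. The check counts measurement occasions per domain and asks what each count can identify.

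**Occasions per participant after enrollment** (Table 1, the Methods and design text, Follow-up outcome measures):

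| Domain | Baseline | 12 weeks | Occasions |
|---|---|---|---|
| Brain imaging | yes | no | 1 |
| Behavioral tests | yes | no | 1 |
| Symptoms | yes | yes | 2 |
| Function | yes | yes | 2 |

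Table 1 also shows coping and observer-rated function at follow-up, which the Follow-up outcome measures section does not list. That difference has no bearing here, since neither place includes a scan or a behavioral test.

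**Subgroup reliability.** Write a circuit measure for person i at time t as Y(i,t) = mean + s(i) + e(i,t), where s is the lasting part and e the occasion-specific part. Reliability over time is Var(s) / [Var(s) + Var(e)]. With one occasion only the sum Var(s) + Var(e) is observed, so the ratio is not identified. The same holds for kappa or any agreement index on subgroup or cluster membership, which needs two classifications per person. Enrolling 160 people, or more, does not change this.

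**Stability of relationships.** Let B be brain, P behavior, S symptoms and F function, with 1 for baseline and 2 for 12 weeks.

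- Brain-behavior: B1 with P1 can be estimated. B2 and P2 do not exist, so there is no second estimate for comparison.
- Brain-symptom: B1 with S1 and B1 with S2 can be estimated. B2 with S2 cannot.
- Brain-function: B1 with F1 and B1 with F2 can be estimated. B2 with F2 cannot.
- Symptoms and function alone: S1 with S2 and F1 with F2 can be estimated.

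Comparing B1-S1 with B1-S2 shows whether a baseline circuit measure still relates to symptoms 12 weeks later. It does not show that the circuit measure, or the subgroup built on it, stayed the same. Treatment between the visits is recorded but not controlled (Methods and design), so a changed association could not be attributed to subgroup instability.

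**Could this be an artefact of a broken table?** No. The running text says that follow-up re-assesses the symptom and functional measures, the separate list of 12-week instruments agrees, and the Statistical analysis section refers only to imaging at baseline. No section mentions a second scan or repeated behavioral tests.

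**The case against.** The strongest reply is that the operative sections are already coherent. No primary objective mentions a retest of subgroups, the Secondary objective is prediction, and item 4 of the Statistical analysis section applies its repeated-measures and reliability models to symptoms and function. This stands. The analysis section is not itself in error and already describes the imaging analysis as prediction. The mismatch lies between those sections and the stated purposes in the Abstract and in Methods and design.

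A second reply is that stability can be read more loosely, as a baseline brain measure relating similarly to symptoms and function at both times. That is a legitimate, weaker reading of aim (c), and the data support it. It does not rescue subgroup reliability or the brain-behavior link.

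A third is that test-retest in the title of Table 1 is merely loose. It does fit the symptom and function rows, but not imaging or behavior.

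Nor can the point be deferred to a fuller plan. The article fixes both the purpose and the follow-up measures, and an analysis plan cannot supply a scan that is not scheduled.

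A reader might go further and infer that aim (c) and the follow-up as a whole have no data behind them. The documents do not support that: symptoms and function are measured twice, and prediction of function, the second purpose in the Abstract, is answerable. A reader might also infer that subgroup reliability is promised throughout. Only the Abstract's Methods and design paragraph promises it; the other places speak of relationships.

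**Conclusion.** The point holds in a limited form. Two stated properties cannot be estimated: the reliability over time of brain-based subgroup membership, and the stability over time of the brain-behavior relationship. The reason is structural, namely one imaging occasion and one behavioral occasion per participant. The primary objectives, the sample size and the baseline analyses are unaffected.

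The conclusion rests only on the schedule as the article describes it, with no numerical assumption. A reader might want to know how often people would change subgroup on a second scan. That would need an assumed retest correlation and an assumed cut-point. The plan gives no retest correlation and fixes no cut-point for high versus low, so no such percentage belongs to this finding.

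**What to change.** 1. In the Abstract (Methods and design), replace the subgroup-reliability purpose with prediction of 12-week symptoms and function from baseline circuit measures, to match the Secondary objective and Statistical analysis sections.
2. In aim (c) of the Abstract and in the main Methods and design section, limit stability to symptoms, function and their relation to baseline imaging.
3. In the title of Table 1, limit the test-retest label to the symptom and function measures.
4. State plainly that temporal stability of the brain-based subgroups is not tested.

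The cost is a few sentences, with no rescanning and no change to the planned analyses.

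Optionally, report split-half reliability of the region-of-interest betas and bootstrap stability of cluster membership from baseline data. Label them as within-session and sampling stability, since neither measures stability over 12 weeks. For the faces task the blocks repeat five times, so an odd/even split would be uneven (3 versus 2). These analyses are small additions to data already collected and are not needed to resolve the point. If the sponsor wants to keep the reliability aim, imaging would have to be repeated at follow-up, at least in a subsample; keeping brain-behavior stability would also require repeating the behavioral tests. That is a far larger commitment.

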**Discussion:**

This project is designed to advance knowledge toward a neural circuit taxonomy for mental disorder. Data will be shared via the RDoC database for dissemination to the scientific community. The clinical translational neuroscience goals of the project are to develop brain-behavior profile reports for each individual participant and to refine these reports with therapist feedback. Reporting of results is expected from December 2016 onward.

**Trial registration:**

ClinicalTrials.gov Identifier: NCT02220309. Registered: August 13, 2014.

## Background

Globally, one in 13 people suffer from clinical anxiety and about one in 21 suffer from clinical depression [1, 2]. Anxiety and depression are the leading causes of disability and lost productivity worldwide [3]. Despite these alarming statistics, we still lack a valid classification system that links underlying neural mechanisms to individual symptoms, real-world functional consequences and the implications for treatment choices. In the current diagnostic system, the Diagnostic and Statistical Manual, fifth edition (DSM-5) [4] the broad categories of anxiety and mood disorders offer a reliable terminology for communicating between clinicians. The DSM-5 (and earlier editions) is not designed to reflect valid categories in terms of underlying neural function. At least 50 % of people have concurrent diagnoses from more than one category of anxiety and mood disorder [5–7]. Due to the heterogeneity of these categories, it is also possible for two people to both be diagnosed with an anxiety disorder but share only one symptom, and the same is the case for depressive disorders. Individuals diagnosed with anxiety and depressive disorders, and their comorbidity, are also commonly treated with the same medications or behavioral therapies [8], reflecting our limited understanding of the distinct underlying mechanisms that could serve as targets for each intervention.

The National Institute of Mental Health has launched the Research Domain Criteria (RDoC) initiative, which is intended to advance the validity of mental disorder classification by incorporating neuroscience [9, 10]. The ultimate goal of the RDOC initiative is to incorporate neuroscience in ways that will bridge the gap between research and clinical decision-making by helping to define cohesive subgroups relevant to treatment selection and to identifying targets for new interventions. The RDoC initiative is aligned with the vision for precision psychiatry [11] and offers an opportunity for an integrative understanding of mood and anxiety disorder [12].

Supported under the RDoC initiative, the present study is aimed at advancing a brain circuit-based taxonomy relevant to the spectrum of anxiety and depression. Brain imaging research in anxiety and depression has identified core nodes of large-scale circuits that are dysfunctional in these disorders. Here our primary focus is on two large-scale neural circuits found to be relevant to the phenotypes of anxiety and associated mood disorders [11]: the “negative affect” circuit and the “cognitive control” circuit (Fig. 1).

**Fig. 1 Fig1:**
[figure not shown]
Summary of negative affect and cognitive control circuits and the proposed extremes of dysfunction within these circuits

### “Negative affect” circuit

The negative affect circuit is engaged by negatively valenced stimuli and comprises subcortical nodes in the amygdala, brainstem regions, hippocampus and insula and both dorsal and ventral prefrontal nodes – dorsal medial prefrontal cortex (dmPFC) and dorsal ACC connections as well as ventral mPFC (vMPFC) and ventral (subgenual and pregenual)-rostral ACC connections [13, 14]. Dorsal/rostral nodes have been preferentially implicated in appraisal and expression of emotion and may be considered an “aversive amplification” sub-network [14] whereas the ventral nodes are implicated in automatic regulation of negative emotion [13, 15]. These sub-networks may be engaged even in the absence of conscious sensory awareness, via direct brainstem inputs [16] (for meta-analysis [13]). In light of their commonly observed co-activation [13], the negative affect circuit could subserve the perception of negative emotion cues and the salience circuit, the arousal aspects of feeling these emotions.

### “Cognitive control” circuit

The “cognitive control” circuit comprises the dorsolateral prefrontal cortex (DLPFC), anterior cingulate cortex (ACC), dorsal parietal cortex (DPC) and precentral gyrus [11]. Together these regions and their interconnectivity are implicated in the support of higher cognitive functions such as working memory and selective attention (for meta-analysis [17]), evidence from convergent neuroimaging methods [18]). Under task-specific demands the cognitive control circuit is implicated in cognitive flexibility [19].

In the current study we use these circuits as the independent (rather than dependent) variable to parse neural circuit-based types of dysfunction in a trans-diagnostic manner. We conceptualize types that represent extremes along dimensions of dysfunction within these circuits and their interactions.

### Proposed types of dsyfunction in the “Negative affect” circuit

We hypothesize that negative affect circuit dsyfunctions will be expressed as hyper-reactivity in the bottom-up innervation of the amygdala and insula at one extreme and loss of top-down regulation of emotion-elicited reactivity at the other extreme (Fig. 1). These putative biotypes may contribute to subjectively experienced phenotypes of “negative bias” and “threat dysregulation” [11].

Amygdala hyper-reactivity elicited by non-conscious processing of masked threat stimuli has been reported in current depressive disorder (for review [20]), generalized anxiety disorder [21], generalized social phobia/anxiety disorder [21–23], specific phobia [24] and panic disorder [21, 24]. Mood-congruent hyper-reactivity of the amygdala has also been observed in response to sad faces [25, 26]. By contrast, the opposite finding of *reduced* amygdala activation for positive expressions has been observed in depressed people [27, 28]. There are also findings of amygdala hypo- (rather than hyper-) reactivity for threat stimuli, which may characterize unmedicated participants who go on to respond to typical first-line antidepressants [27, 29].

Correspondingly, ACC hypo-activation during the processing of threat stimuli has been observed in generalized anxiety disorder [15, 30] and generalized social anxiety [30]. Reduced connectivity between the amygdala subgenual/ventral ACC has been observed during the processing of masked threat stimuli in unmedicated MDD [31], generalized social anxiety disorder [32] and generalized anxiety disorder [15].

### Proposed types of dsyfunction in the “Cognitive Control” circuit

We hypothesize that cognitive control circuit dsyfunctions may also be expressed as hyper-reactivity at one extreme and hypo-activation reflecting loss of top-down control at the other extreme. These putative biotypes may contribute to subjectively experienced phenotypes of “cognitive overdrive” and “cognitive dyscontrol” [11] (Fig. 1).

Depressed people show hyper-activation of the DLPFC during working memory and executive function tasks, which may reflect an attempt at compensation to retain normal behavior (Fig. 1). DLPFC hyper-activation has been observed during tasks with an increasing cognitive demand, but in the absence of performance deficits, in, medicated MDD [33] and unmedicated MDD [34]. Hyper-activation of the ACC has also been observed in MDD when participants are performing similarly to controls (rostral ACC [33]) and this effect persists after remission.

Dysfunction of the cognitive control circuit may be elicited by tasks requiring effortful selective processing of relevant while inhibiting irrelevant stimuli, and suggests a “cognitive loss” type (Fig. 1). Hypo-activation of the DLPFC and dorsal anterior cingulate cortex (dACC) has been observed across diagnoses, including depression [35–37] and social anxiety [38]. Correspondingly, depression has been associated with a loss of functional DLPFC-dACC connectivity when cognitive control is required [36]. Hypo-activity in these nodes of the cognitive control circuit has been found to persist after recovery in adult and later-life depression [39] suggesting that a “cognitive loss” type may have a trait-like status.

### Linking brain circuit dysfunction to symptom profiles

It is not yet known how dysfunctions involving the negative affect and cognitive control circuits relate to specific features of anxiety and mood symptoms. Here we assess multiple features of anxiety, depression and general distress, encompassing constructs of “anxious arousal”, “apprehensive expectations” (and rumination) and anhedonia. Paralleling the findings for brain imaging of neural circuits, a wide range of disorders share common symptoms. For example, multiple anxiety disorders (e.g., specific phobia, panic and social anxiety) share symptoms of anxious arousal (implicating dysfunctions in bottom-up threat reactivity), while other general and trauma-related anxiety disorders (GAD and PTSD) are accompanied by more cognitive experiences of anxiety, such as apprehensive expectations (implicating lack of emotion regulation) [40, 41]. Data-driven techniques such as factor analysis may be useful in identifying specific dimensions of symptoms that cut across traditional diagnoses [42].

The RDoC Anxiety and Depression (“RAD”^1^) study is supported by the NIMH RDoC initiative, and designed to make progress toward a cohesive brain-based taxonomy relevant to the spectrum of anxiety and associated mood disorders and associated impairments in behavior and real-world function.

## Research objectives

### Primary objectives

To use brain imaging to identify cohesive transdiagnostic dimensions of dysfunction in the “negative affect” circuit for threat reactivity and regulation, and associated dysfunctions in the “cognitive control” circuit. We will also assess interactions between these brain circuit dysfunctions.To assess whether brain circuit-defined dysfunctions relate to the severity of specific anxiety and mood symptoms, such as anxious arousal and apprehensive expectations.To assess whether these brain circuit-defined dysfunctions also relate in a cohesive way to behavioral performance and to real world functions related to burden of illness, specifically social functioning, quality of life and work productivity.

